**Intervention group**

Participants in the intervention group will be given clear, accessible instructions on how to use the tests (this will be communicated to them and provided on a written document). Participants will be instructed to call a phone hotline that we will establish in the event of any adverse events that they or their sexual partners experience. They willalso be given a list of places that partners can access for confirmatory testing and advisedto encourage their partner to go for confirmatory testing.

They will be also receive information about HIV self-testing including reasons for suggesting usage of the self-test to their partner and strategies for introducing self-tests to their partners; however, it will also be emphasized that women are under no obligation to suggest to their partner or convince him to use the self-test. Because use of self-tests at home will mean that a trained counselor will not be present when women or their partners take the test, we will develop messages that can be communicated to women easily so that they and their partners can use the self-tests correctly and safely on their own. The messages and counseling that we will provide will adhere to Kenya’s National Guidelines for HIV Testing and Counseling [16].

Two self-test kits will then be distributed to women, each containing the following:

- One standard OraQuick ADVANCE I/II test kit with developer fluid vial and stand;
- Written pre-test information including test instructions in written and pictorial form, post-test counselling information and details about how and where to access HIV confirmatory testing in or near Kisumu;
- Aphone number that participants can call to obtain additional information about taking the test, interpreting results, obtaining referral information,post-test counseling or obtain help in case of IPV.
- Two voucherswith unique identifying numbers which can be redeemed at confirmatory testing for a small token.

All the information above will be communicated orally to women initially and also provided in written form ofan information sheet, in English, Kiswahili and Luo.

**Control Group**

The control group will get standard of care ante/post-natal care as per the MoH guidelines whereby pregnantwomen are encouraged to learn their HIV infection status, as well as that of their sexual partners.For postnatal women, HIV counseling and testing is usually offered to all women with unknown HIV status. In the study, all women in the control group will be given referral coupons with unique identifying numbers which they (and their partners) can redeem at a VCT center for a small token. Participants will be encouraged to go to one of the study facilities for HIV testing.

**Follow-up interviews**

Follow-up interviews with participants in the control and intervention groups will be conducted by trained counselors 3 months after enrollment in order to learn about decision-making regarding partner or couples testing. In the control group, we will obtain information from participants on whether they asked their partner to accompany them to the ANC and use the referral voucher for voluntary HTC. In the intervention group, we will obtain information from participants on whether they suggested usage of the self-test to their partner, whether their partner used the self-test, and whether the couple used self-tests together (with mutual disclosure of HIV status) or if instead the partner was believed to have used the self-test alone. In cases where self-tests were reported to have been used, trained HTC counselors will also ask to see the self-tests and obtain visual confirmation of usage. We will also obtain self-reported information on whether partners who used self-tests sought confirmatory testing (those who did not but wish to have their results confirmed during the visit will be tested by the counselor) and whether partners who obtained an HIV-positive test result sought care at an HIV clinic.

In both groups, we will ask participants whether their partners have accompanied them for ANC or PPC visits in the past 3 months. We will also ask participants if their partners have sought care at an HIV clinic in case an HIV-positive test result was obtained. Finally, in both groups, we will inquire about adverse eventssuch as reports of verbal abuse or physical violenceduring the follow-up interview; those who report events will be referred for support. The study will provide a 24-hour hotline that participants can call with questions or to report an adverse event. The hotline will be staffed by trained study personnel who will be available to counsel and provide referrals to participants. If any adverse events are reported, they will immediately be reported to the Ethical Review Boards and action will be taken where possible.

**Recording uptake of voluntary HTC (control group)**

At the time of enrollment participants in the control group will be provided with referral vouchers (with a unique participant ID code) for HTC (at LHC or another facility of their choice within and around Kisumu) that they and their partners can use for either partner testing (partner tests alone) or couples testing. In the 3 months after enrollment, we will be able to clearly determine whether participants’ partners came for HTC either individually or as a couple based on whether the referral vouchers were presented at HTC sites.

Research assistants at LHC, KEDH and Rabuor Health Centrewill collect and record the referral voucher numbers (with a unique participant ID code) presented at the HTC sites when an individual comes for HIV testing. They will record whether participants’ partners presented these vouchers in the 3 months after enrollment in order to obtain information on utilization of testing by both intervention and control groups. This strategy has been successfully implemented in previous studies that our team has conducted in the Nyanza region of Kenya, including impact evaluations supported by the Gates Foundation and 3ie in which we record uptake based on presentation of referral vouchers.

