### Primary Outcome Measures

The primary outcome for the study will be uptake of HIV testing by women’s partnerswithin 3 months of enrollment in the study. For each participant, we will record whether the participant’s partner underwent HIV testing – in the case of the intervention group, this will be a report by female study participants that their partner used a self-test; in the control group, this will be uptake of HTC at the VCT by the partner. We will test for differences in the primary outcome variable between the intervention and control group.

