# STUDY DESIGN

## Overview of study design

To determine the impact of the intervention on partner or couples HIV testing, the project will use a randomized controlled trial design.

We will recruit about 600 adult womenfrom antenatal and postpartum careclinics. Participants will be randomized to one of two groups: intervention or control.

Following a baseline interview, participants in the intervention groupwill be shownhow to correctly use theself-tests and given two HIV self-tests. Subsequently, we will contact participants periodically over a 3 month period to see if they have used the test(s) with their sexual partners and conduct a follow-up interview.

Following the baseline interview, participants in the control group will be given referral vouchers for themselves and their partners to obtain HIV testing at VCT centers. We will contact the participants at the end of 3 months to see if they and/or their partner(s) have sought HIV testing.

We will also conduct in-depth qualitative interviews with a subset of study participants in the intervention group, including participants who have used HIV self-tests together with their partner, those who have used the test [partner testing] and those who have not used HIV self-tests.

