**Utilization of confirmatory testing (intervention group)**

In the intervention group, participants will be provided with referral vouchers (with a unique participant ID code) that they and their partners can use for confirmatory testing (at any of the three study facilities or another facility of their choice within and around Kisumu). We will record whether participants’ partners presented these vouchers in the 3 months after enrollment in order to obtain information on utilization of confirmatory testing.

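### Voucher presentation cannot separate partner-alone from couples testing in the control arm, so the control side of two secondary outcomes would be misclassified

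*Protocol*

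**What the plan says.** Under Overview of study design, "participants in the control group will be given referral vouchers for themselves and their partners to obtain HIV testing at VCT centers". Under Control Group, these are coupons with identifying numbers "which they (and their partners) can redeem at a VCT center for a small token".

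Under Recording uptake of voluntary HTC (control group), women receive "referral vouchers (with a unique participant ID code) for HTC". The same vouchers may be used whether the partner tests by himself or the two test as a couple. The protocol then says it will be clear whether the partner came "either individually or as a couple based on whether the referral vouchers were presented at HTC sites". Research assistants at the three study facilities log voucher numbers each time a person attends for a test, and they record whether the participant's partner presented the voucher. Vouchers may also be used at other facilities in the Kisumu area.

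Under Secondary Outcome Measures, partner testing and couples testing are two separate outcomes to be compared between arms. Couples testing requires that both members receive counselling, testing and results jointly, so that each learns the other's status. Partner testing is separate testing of the man, where mutual disclosure need not follow. The list under Follow-up data repeats both as items 3 and 4, for each group.

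Under Primary Outcome Measures, "in the control group, this will be uptake of HTC at the VCT by the partner".

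**The concern.** The definition of couples testing turns on what happened during the visit. The stated rule looks only at whether vouchers were handed in. If the rule is followed, men will be placed in the wrong one of two categories that the protocol reports separately and compares between arms.

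The comparison is also uneven. Under Follow-up interviews, intervention women are asked whether the couple used the self-tests together with mutual disclosure or the man used one alone. The items listed there for control women are whether they asked the partner to come and use the voucher, and, as in both arms, whether he accompanied them to clinic visits. Neither is a question about testing together. A difference between arms in couples testing could then reflect how it was recorded rather than what couples did.

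**Working it through.** The protocol states no figure on this point to reproduce. The check is whether the described record can tell the two kinds of testing apart.

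**Inputs**
- Voucher holders: the woman and her partner (Overview of study design; Control Group).
- Voucher identifier: a number with the participant's ID. No section says whether the woman's and the partner's vouchers differ.
- Recorded at the three facilities: voucher number, and whether the partner presented it (Recording uptake of voluntary HTC).
- Not described anywhere: date of each redemption, joint attendance, joint counselling, joint results.
- Definition to be met: joint counselling, testing and results (Secondary Outcome Measures).

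**Attendance patterns set against the record**
1. The woman tests one day and the man tests alone another day. Record: two vouchers, partner presented one. By definition: partner testing.
2. The two attend, test and hear results together, handing in two vouchers. Record: two vouchers, partner presented one. By definition: couples testing.
3. The man attends alone. Record: one voucher, partner presented. By definition: partner testing.
4. The two attend, test and hear results together, and he hands in one voucher. Record: one voucher, partner presented. By definition: couples testing.

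Patterns 1 and 2 leave the same record, and so do patterns 3 and 4. Any rule built on presentation must give the same answer within each pair, so it is wrong for one member of each. Knowing that the man presented does not help, because he did so in all four.

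**Other sources for control women**
- Overview of study design: at 3 months women are asked whether they and/or their partners sought testing. This does not establish that they tested together.
- Limitations: women in both arms report whether the partner tested by any route. This does not separate alone from together.

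**Scale**
- Sample size justification: 300 control women, 20% expected uptake of partner or couples testing. Expected control partners tested = 0.20 × 300 = 60.
- Weight of one misplaced man = 1/300 = 0.33 percentage points, taken from one proportion and added to the other.
- Outer bound if all 60 were misplaced in one direction = 60/300 = 20 points. This is a bound, not an estimate. The documents give no basis for a misclassification rate.

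**Effect on the primary outcome**
In all four patterns the man tested. Where he is recorded as presenter, moving him between categories leaves the primary outcome unchanged.

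**The case against.** The strongest reply is that the protocol does record who came. The section on recording uptake says research assistants note whether the partner presented the voucher, and the section on confirmatory testing in the intervention group says the same of its vouchers. Participants are women and the partners studied are men, so a research assistant collecting a voucher in person can see who is there. The primary outcome counts only the partner's test. The coupons also carry identifying numbers, which could differ between the woman and the man.

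This reply stands for the primary outcome at the three study facilities. A reader might infer that vouchers do not show who tested at all, that a woman redeeming her own voucher for the token would be counted as her partner, and that trial power would fall sharply. The documents do not support that reading. It requires the presenter record to be ignored, and any power loss would rest on redemption shares found nowhere in the protocol, so no such figure is given here. Nor does the problem carry over to the listed confirmatory-testing outcome. Intervention women do receive vouchers "that they and their partners can use for confirmatory testing", but item 7 under Follow-up data is the woman's own report.

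A second reply is that the couples split may come from the follow-up questionnaire, which is an appendix not shown, and that mutual disclosure is itself a listed follow-up statistic. That is possible. But the protocol names voucher presentation as the control-arm source, and the interview content it describes gives the together-or-alone question only to intervention women. Mutual disclosure alone does not show that the two tested together.

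A third reply is that voucher codes and tablet fields belong in operating procedures. That would answer an omission. Here the protocol states a rule that cannot deliver its own definition.

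**Conclusion.** The concern holds for the split between partner-alone and couples testing in the control arm. The stated rule cannot yield couples testing as the protocol defines it, and followed as written it would misclassify the control side of two between-arm secondary outcomes. The size cannot be estimated from the documents. At planned uptake it concerns the classification of about 60 control partners, at 0.33 points each.

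The primary outcome is exposed only where the presenter is not identified. The clear case is a facility other than the three study sites, where vouchers may be used but no research assistant is described.

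The conclusion assumes that the record consists of what the protocol describes. If the unseen follow-up questionnaire already asks control women whether they tested together and received results together, a usable source exists, and the sentence on vouchers should be changed to point to it.

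**What to change.** In the section on recording uptake in the control group:
- Give the woman's and the partner's vouchers distinct codes under the participant's ID.
- For each redemption, have the research assistant record who presented it (woman, partner or both), the date, and whether the two were tested and given results together.
- Classify couples testing from that last field, and remove the statement that presentation alone determines it.
- State how the presenter will be identified when a voucher is used outside the three study facilities, or that such redemptions are not captured.

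In the section on follow-up interviews, ask control women the together-or-alone question already asked of intervention women, so that the two secondary outcomes have a common self-reported source in both arms.

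The cost is voucher printing, a few tablet fields and one interview item. The coding and fields need to be in place before vouchers are issued, because joint attendance cannot be recovered afterwards from voucher numbers.

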# LIMITATIONS

This study has several limitations that warrant discussion. We recognize the limitations of relying on self-reported HIV testing as an outcome variable. This is an inherent issue in all studies to date that have measured the use of self-tests, since the self-tests are typically used in private. We will take several steps to overcome the limitations of having self-reported outcomes in the intervention group and an objective outcome in the control group. First, in the intervention group, during the follow-up interview we will ask to see the used self-testing package in cases where study participants report that they or their male partner used the self-test (this has previously been done in other studies in Malawi). While the verification of used self-testing packages is not necessarily a flawless measure of actual usage of self-testing, it will provide some indication of how much higher the self-reported measure is relative to the verified measure. Second, we will also explore ways to verify whether the participants’ partner sought confirmatory testing after using the self-test: If the participant states that their partner went for a confirmatory test, we will check whether the referral voucher given to them were recorded at the VCT that they visited.

In comparing the intervention and control groups, we will also examine a self-reported outcome that will be similar in both study arms so as the reduce bias in the estimated effect of the intervention: in particular, we will ask study participants in both groups to self-report whether or not their partner tested for HIV through any modality after enrollment in the study (either in clinic or with self-testing). By virtue of being self-reported and comparable in both study arms, this will enable us to determine if the intervention resulted in higher reported HIV testing for ther partners of study participants. We believe that when we triangulate all this information, we will be able to make a more accurate determination of whether the intervention is effective in promoting HIV testing.

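### Control vouchers may be used at any facility in and around Kisumu, but recording is described at only three, so control partners who test elsewhere may be scored as untested in the primary outcome

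*Protocol*

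**What the plan says.** All references are to the Protocol.

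- **Primary outcome.** Primary Outcome Measures defines the outcome separately by arm. In the intervention arm it is the woman's report that her partner used a self-test. For the other arm it says: "in the control group, this will be uptake of HTC at the VCT by the partner". Limitations describes the intervention outcome as self-reported and the control outcome as objective.
- **Where control vouchers can be used.** Recording uptake of voluntary HTC (control group) allows use "at LHC or another facility of their choice within and around Kisumu".
- **How control testing is established.** The same section says the study can determine clearly whether partners came for testing, "based on whether the referral vouchers were presented at HTC sites".
- **Who records.** The next paragraph gives the only stated process: "Research assistants at LHC, KEDH and Rabuor Health Centrewill collect and record the referral voucher numbers". No recorder or transfer of records is described for any other facility.
- **Steering.** Control Group says: "Participants will be encouraged to go to one of the study facilities for HIV testing". This is encouragement, not a condition of the voucher.
- **Confirmatory testing, intervention arm.** Utilization of confirmatory testing (intervention group) makes those vouchers usable "at any of the three study facilities or another facility of their choice within and around Kisumu". Under Limitations, where a woman reports a confirmatory test, "we will check whether the referral voucher given to them were recorded at the VCT that they visited".
- **Supplementary measure.** Limitations also plans to ask women in both arms whether the partner tested by any modality, in clinic or with a self-test.

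**The concern.** The facilities where the control arm may test form a wider set than the facilities where its tests are described as being captured. A man who uses his voucher at a fourth site has done what the protocol invites him to do, yet no stated process records it. If the primary outcome rests on vouchers, he counts as untested.

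The loss runs in one direction. Missed voucher use lowers the control count, while a woman's report of self-test use is unaffected by where any clinic is. Unlike sampling error, this does not shrink with a larger sample. The protocol's own Introduction makes testing elsewhere plausible: it says testing is free in most places and lists inconvenience and transport cost among the barriers.

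This is separate from the arms having different outcome definitions. The voucher register would be incomplete even if both arms were measured by voucher.

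**Working it through.** **1. The plan's own figure.** Inputs from Sample size justification: 20% versus 30%, 300 per group, 80% power. Two-sided alpha of 0.05 is from Statistical analysis, which states it for the other comparisons; I assume it applies to the primary test too.

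n per group = [1.960·√(2·0.25·0.75) + 0.842·√(0.2·0.8 + 0.3·0.7)]² / 0.10² = (1.200 + 0.512)² / 0.01 ≈ 293.2, rounded up to 294. Power at 300 per group is 80.9%. The stated 300 is reproduced, without continuity correction and before any design effect. The present point does not depend on this figure, which only supplies a scale.

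**2. Voucher validity against voucher capture.**

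| Use of voucher | Accepted at | Recording described at |
|---|---|---|
| Control arm, partner or couples testing | LHC or any other facility in and around Kisumu | LHC, KEDH, Rabuor |
| Intervention arm, confirmatory testing | The three study facilities or any other in and around Kisumu | Recording is promised, but no process beyond the three is stated |

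The first row feeds the primary outcome. The second does not. Secondary Outcome Measures and Follow-up interviews also collect confirmatory testing by self-report, so there only the voucher verification in Limitations is affected.

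**3. Illustration of size.** The documents do not give the share of control partners' tests done elsewhere, so it is varied here. Assumptions: true uptake across all facilities is 20% in each arm (60 of 300), there is no true difference, the intervention arm is fully captured, and fourth-site tests are scored as untested.

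Let s be the share of control tests done at a recording facility.
- Recorded control rate = 0.20·s.
- Apparent odds ratio = (0.20/0.80) / [r/(1−r)], with r the recorded control rate.
- Chance of a significant result favouring the intervention = Φ{[d − 1.96·√(2p̄(1−p̄)/300)] / √[(r(1−r) + 0.2·0.8)/300]}, with d = 0.20 − r and p̄ the mean of the two rates.

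Worked case, s = 0.75: r = 45/300 = 0.15, d = 0.05, p̄ = 0.175. Then (0.05 − 1.96·0.03102)/0.03096 = −0.35, and Φ(−0.35) ≈ 0.36.

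| Tests elsewhere | Recorded control | Shortfall | Apparent OR | Chance of false significance favouring intervention |
|---|---|---|---|---|
| 0% | 60/300 = 20% | 0 points | 1.00 | 2.5% |
| 10% | 54/300 = 18% | 2 points | 1.14 | 9% |
| 25% | 45/300 = 15% | 5 points | 1.42 | 36% |
| 40% | 36/300 = 12% | 8 points | 1.83 | 76% |

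If the truth were 20% versus 30% (OR 1.71), the same leaks would give observed differences of 12, 15 and 18 points (OR 1.95, 2.43 and 3.14).

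**4. Limit of the illustration.** Sample size justification states its 20% for testing at LHC, which is itself a recording site. That figure is therefore not an all-facility rate, and the table does not predict what this trial will record.

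**The case against.** - **Three-site recording is inferred from silence.** The protocol never says vouchers will be recorded at three sites and nowhere else. Secondary Outcome Measures speaks of several VCT clinics where confirmatory testing can be recorded, the confirmatory section promises recording with no site limit, and Limitations refers to the record at whichever VCT was visited. A reader might infer that fourth-site tests are certainly lost; the text does not support that. What stands is that no process is stated beyond the three, so the claim of clear determination has no basis as written.
- **Much of this is already covered.** The any-modality question in both arms would pick up fourth-site tests, and Overview of study design says control participants will be asked at 3 months whether their partners sought testing. Both would reveal the problem. Neither is the primary outcome, so neither corrects it.
- **The primary outcome may already allow self-report.** Statistical analysis describes the variable as whether the partner was reported to have tested. But Primary Outcome Measures, the voucher section and Limitations together point to a voucher-based control outcome. The ambiguity is a further reason to settle the rule.
- **The shortfall is not the net bias.** The intervention outcome counts self-test use only, so an intervention partner who tests in clinic instead is also missed, which works against the intervention. This stands: the direction given here is for this one source.
- **Confirmatory testing.** A reader might infer that true confirmatory tests disappear, or that women would be labelled over-reporters. Self-report is collected as well, and Limitations says only that the team will explore ways to verify. The effect is confined to verification.

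**Conclusion.** The point holds. The protocol accepts control vouchers more widely than it describes recording them, so its claim that vouchers clearly establish partner testing is not supported. Control partners who test at another facility may be scored as untested in the primary outcome, and bias from this source favours the intervention.

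Its size cannot be stated. The range of 2 to 8 points illustrates an assumed 20% true all-facility uptake with 10% to 40% of tests elsewhere. A reader might take it as an estimate of the bias in this trial, but the documents give no share tested elsewhere and state their 20% for LHC. The conclusion rests on two readings: that the control primary outcome is voucher-based, and that no unstated arrangement captures vouchers at other sites. If such an arrangement exists, describing it would resolve the point.

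**What to change.** Leave voucher validity unchanged. Restricting vouchers to the three sites would close the gap on paper but could lower real control uptake, which also favours the intervention. Instead:

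1. Extend the any-modality question already planned at 3 months in both arms to record whether, and at which facility, the partner tested.
2. State in Primary Outcome Measures and in Recording uptake of voluntary HTC (control group) that a reported clinic test at a non-recording facility counts as partner testing, in both arms. Keep the voucher-only control count as a sensitivity analysis.
3. Exclude tests at non-recording facilities from the voucher check in Limitations, so that a missing record there is not read as evidence against the woman's report.
4. Replace the claim of clear determination with a statement that voucher capture covers the three recording facilities.

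The cost is one added item in the follow-up questionnaire and a protocol clarification. The downside is that part of the control outcome, which Limitations calls objective, becomes self-reported; the voucher-only sensitivity analysis shows how far the result depends on that. The question must be in place before the 3-month interviews, since facility details not collected then cannot be reliably recovered.
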